##### 2. Secondary outcome measures

2.1 *Duration of hospital stay: *number of bed-days for emergency admissions with a primary diagnosis of HF, CLD (*i.e*., COPD, asthma and other respiratory conditions) and other causes during 12 months after randomisation.

2.2 *Number of hospital admissions due to exacerbation of HF and CLD *(*i.e*., *COPD, asthma and other respiratory conditions*) that occurred in a period of 12 months post-randomisation.

2.3 *Mortality rate: *number of all-cause deaths at 12 months. Cause of death will be taken from the primary and/or secondary care clinical records.

2.4 *Level of use of health resources measured during a period of 12 months after randomisation:*

- Number of emergency department visits for a cardiac or respiratory cause and for all causes.

- Number of home visits (by their GP or nurse).

- Number of primary care visits.

- Number of telephone contacts with primary health care professionals.

- Number of visits to the specialist doctors.

2.5 *Cost-effectiveness analysis*. The costs associated with the health care resources used will be estimated based on the following variables: duration of hospital stay, use of emergency services, purchase and maintenance of telemonitoring devices, number of consultations and time of the health care personnel, as well as the time dedicated by the health care professionals to using the telemonitoring equipment. The effectiveness will be expressed in Quality-Adjusted Life Years (QALY) and will be calculated from the data of the Health Related Quality of Life (HRQL) obtained from the generic EQ-5D questionnaire.

2.6 *Health related quality of life (HRQL)*. The validated Spanish version of the EQ-5D questionnaire will be employed for the quality of life assessment [23-25]. This questionnaire describes the health status in five dimensions (mobility, self-care, usual activities, pain/discomfort, and anxiety/depression) with three possible responses for each item and using the visual analogue scale (VAS) ranging between 0 and 100.

2.7 *Other variables of clinical efficacy: number of episodes of worsening of the pulmonary and/or heart condition*. An episode of worsening or exacerbation is defined as a sustained worsening of the patient's symptoms from a usual stable state that is beyond normal day-to-day variations and is acute in onset. Commonly reported symptoms are oedema, breathlessness and nocturia for HF, and worsening breathlessness, cough, increased sputum production and change in sputum colour for CLD. An episode of worsening is considered a change in these symptoms that requires intervention or control by the physician.

2.8 *Functional status*. The Barthel Index (BI) [22] will be used to measure Activities of Daily Living (ADL). The score on the BI ranges between 0 and 100, with results indicating: total dependence (0-20), severe dependence (21-60), moderate dependence (61-90), little dependence (91-99), and total independence (100).

2.9 *Caregiver burden*. The burden of the family/caregiver will be measured using a validated Spanish version of the Zarit Burden Interview (ZBI) [26-28]. The score ranges from 0 (no burden) to 88 (highest level of burden).

2.10 *Degree of acceptance and satisfaction of patients and health professionals*. The degree of satisfaction of the patients with the telemonitoring intervention will be assessed using a questionnaire based on validated published surveys adapted for this study [29-31]. It consists of 18 items grouped in eight dimensions. The patient satisfaction questionnaires will be administered at the patient's home by an independent female sociologist not involved in the care process. The degree of satisfaction of GPs and nurses participating in the intervention group will be assessed through a qualitative study based on focus group methodology and by means of a specific questionnaire designed *ad hoc*. A Web-based version of the questionnaire for health care professionals will be delivered electronically.

2.11 *Evaluation of the technical performance and compliance with the telemonitoring system*.

Compliance with telemonitoring will be evaluated through the analysis of the frequency of data transmitted by patients and the number of times that health care professionals access the telemonitoring Web-platform. Additionally, the reliability and performance of the telemonitoring system will be assessed (malfunctions of the system, problems concerning the transfer, reception and visualisation of data). The security of the system will also be evaluated (external attacks to the transmission system or server, etc.).

The reasons for the *losses *occurred during the study will be recorded. It is envisaged that such losses may include patients moving house or dying, failure to correctly manage the system, technical problems, requirements for specific health care (for example, patients in need of palliative care at home) and institutionalisation. Additionally, data concerning eligible patients or professionals who declined to participate in the study and the reasons for not participating in the study will be recorded.

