## Methods/design

### Main characteristics of the study

#### Study design

This is a randomised controlled trial with a one-year follow-up. In the intervention group (IG), in addition to the standard practice, patients will be monitored using a telemonitoring procedure, while the control group (CG) will receive the usual care. Participants will gradually join the study over a period of six months. The recruitment period could be extended to reach the targeted number of patients. Interim data analysis will be carried out after 3 and 6 months of follow-up and the final results will be obtained at 12 months post-randomisation. Figure 1 outlines the general study design.

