#### Technical features of the system and devices for data transfer and reception

The telemonitoring equipment, supplied by Saludnova [20], consists of a touch screen PDA which runs the Microsoft's Windows Mobile operating system, with wireless Bluetooth sensors to measure blood pressure, heart-rate and oxygen saturation, and manual input of body temperature, respiratory-rate, weight, questionnaires on the medical condition, any perceived changes and a record of compliance with medication and diet. The telemonitoring kit used by patients in the intervention group is shown in Figure 3. The data will be transferred via GPRS to the Web-based platform (Web data manager). The centralised Web management system allows different levels of access depending on the specific roles of the participating professionals (project leaders, GPs/nurses, hospital). The screen of the Web-platform accessed by health care professionals to check the transmitted data is shown in Figure 4. Although the platform can be accessed from any computer connected to the internet, it should be noted that there are terminals available in the consultation rooms of the health centres and in one of the referral hospitals (Santa Marina Hospital), which given its characteristics, often provides care to this type of patients.

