##### 1. Primary outcome measure

*Number of hospital admissions due to any cause that occurred in a period of 12 months post-randomisation*.

The hospitalizations will be classified as due to HF, due to CLD (*i.e*., COPD, asthma and other respiratory conditions) and non-cardiorespiratory causes.

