### Sample size

Thirty patients will be recruited in each of the study groups, the main constraints being the number of available devices and the number of potential patients fulfilling the inclusion criteria in the Bilbao Primary Care Health Region. Thus, if 30 patients are included in each group, and a 10% loss to follow-up is assumed at 12 months (based on previous analysis of mortality and other causes of loss in patients with similar characteristics), we have estimated a statistical power of 72% to detect significant differences between the CG and the IG in the mean number of total admissions with a level of significance of 5%. For the power calculation, it has been assumed that the mean number of admissions in the CG is 3.5, the standard deviation 1.7, and there will be a 35% decrease of hospitalisations in the IG with respect to the CG [32-34]. The power calculations have been performed with the sample size calculation software Ene 2.0.

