#### Description of the baseline characteristics of the patients

The unit of the study is the patient. The following statistics will be used for the descriptive analysis: mean, standard deviation, median and rank for the quantitative variables, and frequency and percentage for the qualitative variables. Socio-demographic and baseline clinical data will be compared between the two groups in order to test the homogeneity. Losses occurring during the study will be analysed and the main baseline characteristics of dropouts will be compared to those who have completed the study. For the comparison of quantitative variables, the Student's t-test and the non-parametric Mann Whitney U test will be used for normally and non-normally distributed data, respectively. The Chi-square or the Fisher's exact tests will be used for the comparison of qualitative variables. The level of statistical significance will be set at p < 0.05.

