### Study limitations

Due to the interactive nature of the intervention, it is not possible to blind the health care professionals providing the intervention or the participants involved in the study. Despite the aforementioned limitation, most of the key data are objective and will be obtained from medical registers (hospital admissions, use of health care resources, etc.). Methods have been put in place to double-check the veracity of the data obtained. Moreover, the statisticians in charge of the data analysis will be blinded to group assignment.

The number of patients included in the present study is limited by the available telemonitoring devices. Despite recruitment of a higher number of patients would have been desirable, we have estimated a power of 72% to detect significant differences in the main outcome measure between the two study groups.

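### Two device-related reasons are classed as losses although only the intervention arm has the device and admissions stay on record, so the randomised comparison may be biased by an unknown amount and direction

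*Protocol article*

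**What the plan says.** The paragraph on losses after item 2.11 (secondary outcome measures) says that reasons for loss will be recorded and that "such losses may include patients moving house or dying, failure to correctly manage the system, technical problems". It then adds the need for specific care, such as palliative care at home, and institutionalisation: six kinds of reason in all.

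Other sections bear on this:

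- **Who has the equipment.** Under Study design, intervention "patients will be monitored using a telemonitoring procedure, while the control group (CG) will receive the usual care". The technical section likewise places the kit with the intervention group.
- **Primary outcome.** "Number of hospital admissions due to any cause that occurred in a period of 12 months post-randomisation".
- **Data source.** Study limitations states that "most of the key data are objective and will be obtained from medical registers (hospital admissions, use of health care resources, etc".
- **Sample size.** Thirty per group, and "a 10% loss to follow-up is assumed at 12 months". The rate is based on mortality and other causes of loss and is not split by arm.
- **Handling of dropouts.** In the section on baseline characteristics, "the main baseline characteristics of dropouts will be compared to those who have completed the study".
- **Unequal follow-up.** The section on the main outcome measure plans incidence rates, including rates of admission, in its descriptive step. The between-group tests it names for quantitative variables are the t-test or Mann-Whitney U.

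**The concern.** A patient who cannot work the PDA, or whose equipment fails, has stopped telemonitoring. That patient has not stopped being observed, because hospital records continue whatever happens to the device. Item 2.11 already measures this behaviour as compliance. Calling it a loss conflicts with an outcome counted from randomisation over 12 months and taken from registers.

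The two device reasons can arise only in the intervention group. If losses drop out of the primary comparison, membership of the analysed set depends on the arm and possibly on prognosis. These are home-care patients with marked functional decline, and the Discussion itself refers to limited computer literacy. Blinding the analysts cannot undo an exclusion that happens in one arm only. With 30 patients per arm, a handful of exclusions is enough to matter.

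**Working it through.** **1. Which reasons are one-sided.** Moving house, death, need for specific care and institutionalisation can occur in both arms. Inability to operate the system and technical problems need a device, so they can occur only in the intervention group. That makes two of six.

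**2. Does the planned power deduct losses?** Inputs from Sample size: control mean 3.5, SD 1.7, 35% reduction, 5% significance (two-sided assumed), 30 per arm, 10% loss.

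- Difference = 0.35 × 3.5 = 1.225.
- Analysed number = 30 × 0.90 = 27 per arm.
- Noncentrality = 1.225 / (1.7 × √(2/27)) = 2.648, which gives noncentral-t power 73.8%.
- With Mann-Whitney efficiency 0.955, effective n = 25.8 and power is 71.8%.
- With all 30 per arm, noncentrality = 2.791 and power is 78.4% (t), or 76.4% with efficiency 0.955.

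The stated 72% is thus reproduced within 2 points when 27 per arm are analysed. This agrees with the section's own words but is no proof of the analysis set. A lower Mann-Whitney efficiency of 0.864 applied to all 30 gives an effective n of 25.9, where power is also about 72%. The power figure itself is not in dispute.

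**3. What exclusion could do.** The documents give neither the number of device-related losses nor the admission rate of such patients, so both are assumed. Take no true effect, with mean 3.5 in each arm. Remove m of 30 intervention patients who average e admissions above 3.5:

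remaining mean = (30 × 3.5 − m × (3.5 + e)) / (30 − m)

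spurious difference = m × e / (30 − m)

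| m | e | Spurious difference | As % of 3.5 | As % of 1.225 | Approximate false-positive rate |
|---|---|---|---|---|---|
| 3 | 1.0 | 3/27 = 0.111 | 3.2% | 9% | 5.7% |
| 3 | 2.5 | 7.5/27 = 0.278 | 7.9% | 23% | 9.3% |
| 6 | 1.0 | 6/24 = 0.250 | 7.1% | 20% | 8.2% |
| 6 | 2.5 | 15/24 = 0.625 | 17.9% | 51% | 26.1% |

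The last column is a two-sided t-test with 30 controls against 30 − m, SD 1.7. If e is negative, the difference has the same form with the opposite sign: m = 3 and e = −1.0 gives 0.111 against telemonitoring.

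The table deletes whole patients. If admissions up to the loss were kept as rates, the distortion would come only from what happens afterwards.

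**4. Power cost of extra one-sided losses.** If 10% are lost in both arms and device reasons remove 3 or 6 more from the intervention arm (assumed), power falls from 73.8% to 71.2% (27 v 24) or 67.9% (27 v 21).

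**The case against.** The strongest reply is that no sentence excludes anyone. The losses paragraph promises only to record reasons, the dropout comparison is an ordinary attrition check, and the 10% is a planning allowance. The incidence rates for unequal follow-up suggest that patients with incomplete follow-up are kept. The article condenses a fuller protocol or analysis plan, where an analysis set may be defined.

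Much of this stands. Removal from the primary test is an inference, and a missing intention-to-treat statement would not by itself be a point to raise. What remains is a classification that the article does state and that conflicts with its own outcome definition and data source. The incidence rates answer only part of it: they belong to the descriptive step, and they would count admissions up to the loss while discarding later ones that the registers hold.

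A reader might go further and infer that the plan compares device-completers with nearly all controls, that the sickest patients leave the intervention arm, and that the result is therefore tilted towards telemonitoring. The documents do not support this. Four of the six reasons apply to controls too, and a single loss rate is assumed for both arms. Technical faults need not track severity, and patients with cognitive impairment are already excluded. An excess of 2.5 admissions is the top of an assumed range. Losing 3 of 30 to device reasons alone would use the whole 10% allowance, and losing 6 would be twice it.

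**Conclusion.** The point holds as a misclassification that puts the randomised comparison at risk. It is not a demonstrated bias. Two reasons that can arise only in the intervention group are called losses, although the primary outcome remains obtainable after either of them. That losses leave the comparison is inferred from the power deduction and the completer contrast.

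If they do leave, the spurious reduction under no true effect is 3 to 8% for 3 exclusions and 7 to 18% for 6. This assumes that those patients average 1.0 to 2.5 admissions above 3.5 and that all their data are dropped. The true size and direction cannot be known from the documents.

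**What to change.** Four changes of wording:

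1. Record device failure or inability to use the system as discontinuation of telemonitoring, reported as compliance under item 2.11, and remove both from the list of losses.
2. State that admissions and the other register-based outcomes are collected for every randomised patient to 12 months or death, and analysed in the allocated arm whatever the device use.
3. Restrict loss to withdrawal of consent for record access or relocation that cannot be traced, with follow-up time as exposure for these patients and for those who die.
4. Present any device-completer analysis as secondary only.

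No new data source is needed, since the registers are already the stated one. The estimate may be less favourable to telemonitoring. Under the plan's inputs, power could rise by up to about 4.5 points (73.8% to 78.4%). The gain is smaller where death cuts follow-up short, because keeping a patient who dies does not restore a full 12-month count. If the fuller protocol or analysis plan already says this, the article needs only to match it.

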### Sample size

Thirty patients will be recruited in each of the study groups, the main constraints being the number of available devices and the number of potential patients fulfilling the inclusion criteria in the Bilbao Primary Care Health Region. Thus, if 30 patients are included in each group, and a 10% loss to follow-up is assumed at 12 months (based on previous analysis of mortality and other causes of loss in patients with similar characteristics), we have estimated a statistical power of 72% to detect significant differences between the CG and the IG in the mean number of total admissions with a level of significance of 5%. For the power calculation, it has been assumed that the mean number of admissions in the CG is 3.5, the standard deviation 1.7, and there will be a 35% decrease of hospitalisations in the IG with respect to the CG [32-34]. The power calculations have been performed with the sample size calculation software Ene 2.0.

### Statistical Analysis

The download, processing and statistical analysis of the data collected during the study will be performed using PASW Statistics 18 software (SPSS). The researchers in charge of the statistical analysis will be blinded to the assignment of the patients to the IG or CG.

#### Description of the baseline characteristics of the patients

The unit of the study is the patient. The following statistics will be used for the descriptive analysis: mean, standard deviation, median and rank for the quantitative variables, and frequency and percentage for the qualitative variables. Socio-demographic and baseline clinical data will be compared between the two groups in order to test the homogeneity. Losses occurring during the study will be analysed and the main baseline characteristics of dropouts will be compared to those who have completed the study. For the comparison of quantitative variables, the Student's t-test and the non-parametric Mann Whitney U test will be used for normally and non-normally distributed data, respectively. The Chi-square or the Fisher's exact tests will be used for the comparison of qualitative variables. The level of statistical significance will be set at p < 0.05.

#### Analysis of the main outcome measure and impact on the use of the health care services

Firstly, at 3, 6 and 12 months follow-up, a descriptive analysis of the primary and secondary outcome measures will be carried out in the two study groups (number of hospital admissions, duration of the hospital stay and mortality rate). The variables related to the use of health care services, clinical efficacy, functional status of the patients (BI), the health related quality of life -HRQL- (EQ-5D) and the family/caregiver burden (ZBI) will also be analysed. Additionally, given that certain variables will have different follow-up periods, the incidence-rates of certain variables, such as mortality, hospital admissions, visits and episodes of worsening will be calculated.

Subsequently, both primary and secondary outcome measures will be compared between the two groups of patients at each follow-up point to test whether significant differences exist. Any changes in the functional condition (BI) or HRQL of the patients (EQ-5D) and caregiver burden (ZBI) with respect to the baseline levels will also be assessed at 3, 6 and 12 months (*i.e*., difference between the follow-up and initial scores). Quantitative variables will be compared using the Student t-test or the non-parametric Mann Whitney U test, while qualitative variables will be assessed using the Chi-Square or Fisher's exact tests. The Student's paired t-test will be used to compare the differences between the baseline scores on the BI, the EQ-5D and the ZBI and the scores obtained at 3, 6 and 12 months follow-up, for each group of patients.

If statistically significant differences are detected between the CG and the IG for the baseline characteristics analysed, the comparisons of the main outcome measures will be adjusted by the corresponding baseline variables. A logistic regression model will be used to compare dichotomous categorical variables (such as, mortality), while a general linear model will be used for quantitative variables (such as, the duration of hospital stay). In the latter case, the dependant variable will be appropriately transformed if it does not fit the normal distribution. Finally, multilevel analysis will be performed to test the effect of the individual primary care professionals involved and the clinical practice site on the results.

Whenever possible, the number needed to treat (NNT) will be calculated for the primary outcome variable (number of hospital admissions).

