Home telemonitoring has been found to reduce rates of hospitalisation and emergency department visits for chronic obstructive pulmonary disease (COPD) patients, while findings for hospital bed days were not consistent and varied between studies [15,16]. There was a higher mortality-rate among patients with COPD using home telemonitoring compared with usual care, but the number of original studies was scarce and the sample sizes were relatively small. Hence, the outcomes must be interpreted cautiously [15,16]. According to recent systematic reviews, telemonitoring interventions for patients with HF have been shown to be effective in reducing the risk of all-cause mortality, HF-related hospitalisations and emergency department visits [15,17-19]. Moreover, the use of home telemonitoring for patients with HF improved quality of life, patient self-care and evidence-based prescribing [15,17-19]. However, further studies of high methodological quality are required to give more precise information about the potential clinical benefits of home telehealth interventions prior to scaling-up the use of the new technology [7,19].

The telemonitoring system used in the present study is based on a telemonitoring system employed in another hospital-based clinical trial [20]. The home telemonitoring system has been successfully tested on patients with HF and COPD in a randomised controlled trial carried out in Donostia University Hospital (Basque Country), *Current Controlled Trials *ISRCTN62033748. In contrast to the aforementioned trial, in the present study the management of the telemonitoring intervention is carried out by primary care nurses and general practitioners (GPs). To the best of our knowledge, no other primary care-based tele-homecare studies have been undertaken with regards to the type of patients and the telemonitoring procedure employed in this investigation.

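### The tests named for the primary admission count carry no follow-up time, although the plan expects follow-up to differ and computes incidence rates descriptively

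*Protocol article*

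**What the plan says.** Under the heading for the primary outcome measure, the protocol article defines the endpoint as "Number of hospital admissions due to any cause that occurred in a period of 12 months post-randomisation". This is a count with no denominator.

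The section on analysis of the main outcome measure proceeds in steps:

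- **Descriptive step.** It recognises unequal follow-up: "given that certain variables will have different follow-up periods, the incidence-rates of certain variables, such as mortality, hospital admissions" and some other event variables are to be calculated.
- **Comparison step.** It then states that "both primary and secondary outcome measures will be compared between the two groups of patients at each follow-up point", and names the tests: "Quantitative variables will be compared using the Student t-test or the non-parametric Mann Whitney U test".
- **Adjusted step.** Only if baseline characteristics differ significantly, "a general linear model will be used for quantitative variables (such as, the duration of hospital stay"), with a transformation if the outcome is not normal.

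No test or model is named for the incidence rates, and no exposure term appears in any of the tests or models. The article lists death among the expected losses (end of the outcome measures section), and the Sample size section includes mortality in its assumed 10% loss.

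**The concern.** The plan identifies the problem and prepares the right quantity, a rate, but does not carry it into the test that decides the trial. A patient who dies in month 2 after one admission counts as a better result than a survivor with three.

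Unequal time at risk is a realistic prospect. The patients are home-bound, with repeated admissions. The exclusion for terminal illness covers only conditions other than HF and CLD. The envisaged losses also include failure to manage the system and technical problems, which only the telemonitoring arm can have. If observation of admissions stopped at such a loss, that arm would lose time even with equal mortality.

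Two things are at stake: a false difference when the arms lose different amounts of time, and lost power even when they do not. There is also a mismatch of target. The hypothesis and the power calculation concern a 35% fall in mean admissions, and Mann-Whitney estimates neither a ratio of means nor a rate ratio.

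**Working it through.** **Inputs from the Sample size section.** 30 per arm; 10% loss, leaving 27; control mean 3.5; SD 1.7; 35% reduction, so the intervention mean is 3.5 × 0.65 = 2.275 and the difference is 1.225; the test is run "with a level of significance of 5"%, taken as two-sided because sidedness is not stated.

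**The plan's own figure.** Two-sample t-test, noncentrality = 1.225 / (1.7 × √(2/27)) = 2.65, which gives power of 73.8%. With 26 per arm it is 72.2%. The stated 72% is reproduced to within 2 points. It is a comparison of means with losses removed and no exposure term.

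**Bias in the raw count.** Assumptions: a fraction *p* of an arm dies, death times are uniform over the year, and patients who die are kept with the admissions they had. Mean exposure is 1 − *p*/2 years, and the expected count is rate × (1 − *p*/2). Mortality by arm is assumed, because the article gives none.

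| Deaths CG v IG | True rates per year | Mean counts | Apparent reduction | Difference |
|---|---|---|---|---|
| 10% v 10% | 3.5 v 3.5 | 3.325 v 3.325 | 0% | 0 |
| 10% v 20% | 3.5 v 3.5 | 3.325 v 3.150 | 5.3% | 0.175 (14% of 1.225) |
| 10% v 30% | 3.5 v 3.5 | 3.325 v 2.975 | 10.5% | 0.350 (29% of 1.225) |
| 20% v 10% | 3.5 v 2.275 | 3.150 v 2.161 | 31.4%, true 35% | 0.989 |

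Dividing by person-time restores the true rate ratio in every row.

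**Effect on the test.** Simulation with 30 per arm, Poisson counts and the same death model. The t-test on raw counts is set against a quasi-Poisson model with a person-time offset. Ranges are over repeated runs, the largest of 40,000 trials.

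| Scenario | t-test rejects | Offset model rejects |
|---|---|---|
| No effect, deaths 10% v 10% | 5% | 5% |
| No effect, deaths 10% v 20% | 5.4% to 6.5% | about 5% |
| No effect, deaths 10% v 30% | 10.4% to 10.9% | about 5% |
| True 35% reduction, deaths 20% v 20% | 66% to 68% | 74% to 76% |
| True 35% reduction, deaths 20% v 10% | 56% to 57% | 75% |

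At 10% v 30%, nearly all the false rejections favour telemonitoring. The fourth row shows the power loss with equal time at risk: truncated counts add variance that the t-test cannot explain.

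**Sensitivity to overdispersion.** With gamma heterogeneity (shape 2), the t-test's type I error at 10% v 30% falls to about 6% to 7%. With a true 35% reduction and 20% v 10% deaths, power is about 29% for the t-test and 41% to 42% for the offset model.

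**The case against.** The strongest objection is that the plan does attend to time at risk. It says follow-up will differ, it plans incidence rates of admissions, and the comparison comes next. A per-patient rate is itself a quantitative variable, so the t-test might be meant for rates. This stands in part: a reader might infer that the plan ignores time at risk, and the text does not support that. But the primary outcome is defined as a count, the power calculation concerns mean admissions, and no test is tied to the rates. A t-test on per-patient rates would also give a patient followed for one month the same weight as one followed for twelve.

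Other stronger readings should also be set aside:

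- **That the arm with more deaths is always credited with fewer admissions.** This needs unequal mortality and patients who die kept with truncated counts. The article counts deaths as losses and removes losses for power, so they may be dropped instead. The fault would then be selection of survivors, with no fixed direction.
- **That telemonitoring will benefit.** The Background does say "There was a higher mortality-rate among patients with COPD using home telemonitoring compared with usual care", but it warns that those studies were few and small, and it reports lower all-cause mortality with telemonitoring in HF. The trial enrols both diseases.
- **That the bias is large.** The 30% mortality is an assumption, well above the plan's 10% total loss. A 10-point gap yields about 5%, against a planned 35%.
- **That the economic analysis is damaged by Mann-Whitney.** It uses per-patient costs, QALYs and bootstrapping.
- **That an offset cures the problem.** When frailty drives both death and admissions, the offset model under no effect at 10% v 30% deaths gave rate ratios from 0.94 down to about 0.78.

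All-cause mortality is already compared between arms, so an excess of deaths would be visible. That helps interpretation but does not correct the primary test.

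**Conclusion.** The point holds in this form: the article foresees unequal follow-up and plans admission rates, but the only tests it fixes for the primary count have no exposure term. This is not a detail left to a fuller document, because the article names the tests.

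If patients with short follow-up are kept, the bias takes the direction of the arm that loses more time. It is about 5% for a 10-point mortality gap and about 11% for a 20-point gap, with t-test type I error of about 6% and 11%. If control mortality is the higher, a real 35% reduction is detected with about 56% power instead of 75%. With equal 20% mortality the loss is about 8 points, in a trial planned at only 72%.

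These sizes rest on assumed mortality, uniform death times, Poisson counts and death unrelated to a patient's own admission rate. Overdispersion reduces the type I error inflation. With equal mortality there is no bias, only the loss of power.

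**What to change.** Make the primary test a rate model of all-cause admissions in all randomised patients: negative binomial or quasi-Poisson, with log(time from randomisation to death, withdrawal or 12 months) as offset. Name one of the two in advance. The plan's SD of 1.7 implies a variance of 2.89, below the mean of 3.5. Quasi-Poisson allows that and negative binomial does not.

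Report the rate ratio with its 95% CI beside all-cause mortality by arm. Use the same model for the other count outcomes (bed-days, visits, worsening episodes), and keep Mann-Whitney as a sensitivity analysis. State that patients who die stay in with their observed time.

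The cost is a change of wording and slightly more analysis work. No new data are needed, since the planned incidence rates already require person-time, and the generalised linear model procedure in the named software fits the model. The remaining weakness is death linked to frailty, which the offset only partly corrects, so the admission result must be read together with mortality.
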